#### Recruitment and data collection

The recruitment strategies include approaching existing pregnant women in participating facilities during prenatal care visits and with website/internet, flyers and local community advertisings. After the identification of potential participants, the research assistant will invite women and obtain an informed consent form of those who meet the inclusion criteria and agree to participate. Maternal age and ethnicity will be recorded from all approached women to facilitate a comparison of those who are recruited and those who decline.

All collected data will preferably be entered directly into the database, but printed forms will also be available in case of inability to access the internet-based database. In such cases, the data will be then entered later and completed printed forms will be stored, according to the required ethical principles.

#### Sociodemographic, physical data and pregnancy outcomes

*First Visit (19–21 weeks):* similarly to the SCOPE study, detailed information of sociodemographic characteristics (age, socioeconomic status, education, ethnicity, occupation and type of maternity care), maternal medical and obstetric history, infertility history, drugs and medications use, family medical and obstetric history and current pregnancy (occurrence and details of infection, vaginal bleeding, dipstick proteinuria, intercourse and hospital admission) will be collected.

Anthropometric measurements of maternal body mass index, height, weight, head circumference, arm circumference and triceps, biceps subscapular and suprailiac skinfolds will be performed according to standardized techniques. Height and weight of lightly clothed women will be measured to the nearest 0.1 mm and 0.1 kg respectively. Head and arm circumferences will be measured with an inelastic tape and skinfold thicknesses will be measured on the same side of the body to the nearest 0.2 mm using Harpenden (and/or Lange) skinfold calliper. The calliper is placed 1 cm distal to the firmly grasped skinfold, using the thumb and the index finger, at 90° to the skin. A single measurement is taken after 2 s.

Dietary intake will be assessed using a 24-h dietary recall administered by a trained professional who will query participants about food and beverage consumption in the previous 24 h. A trained nutritionist will then estimate calories, macro and micronutrient intake using computer-based standard tables allowing for appropriate ethnic, social and regional variations.

Furthermore, three consecutive manual blood pressure measurements will be recorded, using an appropriate cuff size for different arm circumferences and using Korotkoff phase V for diastolic blood pressure.

*Second and third Visit (27–29 weeks and 37–39 weeks; both optional):* three consecutive manual blood pressure measurements, anthropometric parameters (weight, height, head and arm circumference and triceps, biceps, subscapular and suprailiac skinfolds) and occurrence and characteristics of infection, vaginal bleeding, dipstick proteinuria, intercourse and hospital admissions will be recorded.

*Postpartum data:* data will be collected from the participant’s medical record, the prenatal chart and/or from a personal interview with the participant during hospital admission to minimize missing information. The main outcome is spontaneous preterm birth, defined as a birth before 34 weeks of gestational age due to preterm labour or premature rupture of membranes. Secondary outcomes will also be evaluated: spontaneous preterm birth alternatively defined as a birth before 37 weeks of gestational age due to preterm labour or premature rupture of membranes, provider-initiated preterm birth, defined as preterm birth due to medical indication on account of maternal or fetal conditions; pre-eclampsia, defined as having systolic blood pressure ≥ 140 or systolic blood pressure ≥ 90 mmHg after 20 weeks gestation on at least two occasions apart of 20 min, and/or proteinuria (24-h urinary protein ≥ 300 mg or urine dipstick ≥ ++) and/or severe maternal complications [32]; gestational diabetes mellitus according to ADA guidelines [33]; fetal growth restriction (FGR) defined as having birthweight below 10th percentile based on GROW customised birthweight centiles [34]. Clinical data will also be collected regarding the occurrence of preterm labour, cervical cerclage, deep vein thrombosis, infection, vaginal bleeding, dipstick proteinuria, intercourse, hospital admission, deep vein thrombosis during pregnancy and puerperium, and maternal mortality and the use of progesterone and/or pessary, tocolytic, antibiotic for preterm labour or pPROM, corticosteroids for fetal maturation, magnesium sulphate for neuroprotection during pregnancy. The occurrence of severe maternal morbidity and near miss will also be reported according to WHO guidelines [35]. Neonatal outcomes related to neonatal morbidity and mortality will be recorded until newborn discharge or death.

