### Discovery phase

The initial phase of the project consists of a case–control study utilizing data and samples collected for the SCOPE study (Screening for Pregnancy Endpoints study). The SCOPE consortium was an international effort to determine the causes and potential predictors for pregnancy complications and its methodology had already been previously published [27–29]. Briefly, the cohort comprised 5690 healthy pregnant women recruited between November 2004 and August 2008 in New Zealand, Australia, Ireland and United Kingdom. Inclusion and exclusion criteria for the SCOPE study are described in Tables 1 and 2, respectively. Exclusion criteria include major fetal anomaly, chronic hypertension, diabetes, renal disease, systemic lupus erythematous, and antiphospholipid syndrome. These will therefore be the same criteria for the current study.

**Table 1 Tab1:** Inclusion criteria of Preterm SAMBA validation phase – Brazilian cohort

• Singleton pregnancy	
• Nulliparous (no previous delivery ≥20 weeks)	
• Up to 21 weeks of gestational age

**Table 2 Tab2:** Exclusion criteria of Preterm SAMBA validation phase – Brazilian cohort

• Unsure LMP and unwilling to have dating US	• Major Uterine Anomaly
• ≥3 Miscarriages	• Cervical Suture
• Major Foetal Anomaly/Abnormal Karyotype	• Knife cone biopsy
• Essential Hypertension Treated Pre-pregnancy	• Ruptured membranes now
• Mod-Severe Hypertension at booking (≥160/100 mmHg)	• Long term Steroids
• Pre-pregnancy Diabetes	• Low-dose Aspirin
• Renal Disease	• Calcium (>1 g/24 h)
• Systemic Lupus Erythematosus	• Eicosapentaenoic acid (fish oil)
• Anti-phospholipid Syndrome	• Vit. C ≥1000 mg & Vit. E ≥400 UI
• Sickle Cell Disease	• Heparin/LMW Heparin
• HIV or Hep B or Hep C positive	

Extensive sociodemographic and physical data will be collected including age, ethnicity, socio-economic status, dietary and lifestyle questionnaire, parity, BMI (body mass index) and cigarette smoking.

Plasma and serum samples will be collected at 20 weeks of gestation using stringent standard operating procedures designed for metabolomics studies, barcoded and stored at −80 °C within 2–4 h; the timing between collection and freezing will be known for all specimens.

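### The pre-eclampsia outcome is misdefined: both pressure limits are labelled systolic, and the and/or connectors let any single component make a case

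*Protocol article*

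**What the plan says.** The rule stands in the protocol article under *Sociodemographic, physical data and pregnancy outcomes*, in the paragraph on postpartum data. That paragraph states that "Secondary outcomes will also be evaluated" and lists pre-eclampsia among them.

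- **Pressure.** The criterion is "systolic blood pressure ≥ 140 or systolic blood pressure ≥ 90 mmHg after 20 weeks gestation".
- **Repeat readings and first connector.** The pressure must be found "on at least two occasions apart of 20 min, and/or proteinuria".
- **Proteinuria and second connector.** The rule continues with "24-h urinary protein ≥ 300 mg or urine dipstick ≥ ++) and/or severe maternal complications", followed by a citation to reference 32.

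Two other places show how the study treats pressure. At the first visit, three manual readings are taken "using Korotkoff phase V for diastolic blood pressure". Table 2, under *Discovery phase*, writes an exclusion limit as a systolic/diastolic pair: "Mod-Severe Hypertension at booking (≥160/100 mmHg".

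*Ancillary studies* says that the occurrence and severity of pre-eclampsia will be recorded, but gives no other definition.

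**The concern.** There are two separate defects. The first is the pressure label: with both limits called systolic, the lower one absorbs the higher, and diastolic pressure drops out of the rule. The second is the connectors: read in the ordinary inclusive sense, two uses of and/or turn three components into three alternatives. Raised pressure without proteinuria then counts as pre-eclampsia. So does proteinuria without raised pressure, including a single ++ dipstick, because the two-occasion requirement is attached only to pressure.

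The defects reinforce each other. The first makes the pressure component nearly universal, and the second lets that component decide the case. They are also independent, so correcting the label leaves the second untouched.

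At stake is the classification of a named secondary outcome that is also a subject of the ancillary studies and, according to the *Discussion*, of later work on the biobank and database. A biomarker analysis against an outcome that mixes different conditions would be hard to interpret.

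**Working it through.** The article states no figure for this outcome, so there is nothing to reproduce. The check has a logical part, which needs no assumption, and an illustrative part, which does.

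**1. The pressure criterion.** Every reading of at least 140 is also at least 90. Hence (systolic ≥ 140 or systolic ≥ 90) = systolic ≥ 90, and the 140 limit has no effect.

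**2. The connectors.** Let B be the pressure criterion, P proteinuria and C severe complications, each present or absent, which gives 2 × 2 × 2 = 8 patterns.

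- Inclusive reading, B or P or C: every pattern is positive except the one with none present, so 7 of 8.
- For contrast, a conjunctive reading, B and (P or C): 3 of 8.
- The 7 − 3 = 4 patterns that change are B alone, P alone, C alone, and P with C but without B.

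These are counts of patterns, not of women. They show how much depends on the connector, not which reading the sponsor intends.

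**3. How many women the literal pressure criterion would catch.** The cohort size of 1150 comes from the article. The rest is assumed, because the article gives no blood-pressure distribution: mean systolic m of 105 to 115 mmHg (with 100 as an extreme), SD s of 9 to 12, and correlation r between two readings of 0.5 to 0.8, under a bivariate normal distribution.

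With z = (m − 90)/s, one reading meets the limit with probability Φ(z), and both of two readings meet it with probability Φ₂(z, z; r).

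| m | s | r | z | One reading ≥ 90 | Both ≥ 90 | Women of 1150 |
|---|---|---|---|---|---|---|
| 115 | 9 | 0.8 | 2.78 | 0.997 | 0.995 | 1145 |
| 115 | 12 | 0.5 | 2.08 | 0.981 | 0.966 | 1111 |
| 110 | 12 | 0.5 | 1.67 | 0.952 | 0.916 | 1053 |
| 105 | 9 | 0.8 | 1.67 | 0.952 | 0.928 | 1067 |
| 105 | 12 | 0.5 | 1.25 | 0.894 | 0.824 | 947 |
| 100 | 9 | 0.8 | 1.11 | 0.867 | 0.813 | 935 |
| 100 | 12 | 0.5 | 0.83 | 0.798 | 0.684 | 787 |

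Over means of 105 to 115 the range is about 82% to 99.5%. At the extreme mean of 100 it is about 68% to 81%. For women with at least two eligible readings these are lower bounds, since any two occasions after 20 weeks suffice and the other components also qualify alone.

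**4. Where the inflation comes from.** Under the same assumptions, with means of 105 to 115, a single reading of at least 140 has probability 1 − Φ((140 − m)/s). This runs from 0.0001 (m = 105, s = 9) to 0.0186 (m = 115, s = 12), about 0.01% to 1.9%. Almost all of the literal excess therefore comes from the second systolic limit.

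**5. What remains once the label is corrected.** The four patterns in step 2 still change classification. Turning that into a number of women needs the frequency of isolated hypertension, isolated proteinuria and pre-eclampsia in this population. The article gives none of these.

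**The case against.** The strongest reply is that the second systolic is plainly a slip. The figures 140 and 90 have the form of a pressure pair, the study measures diastolic pressure, and Table 2 writes pressure as a pair. A clinician would read through the error. Outcome data come from the medical record, prenatal chart or interview, and the article does not describe a derivation coded from this sentence. This stands: the literal case fraction describes the text, not an expected result.

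A second reply is that this is a condensed article that cites a source for the definition. That only partly helps. The rule is not left out here; it is stated, and the stated rule is wrong. But the cited source is not shown, so the article does not establish which combinations the sponsor means.

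A third reply is that the outcome is secondary. This also stands. The main outcome is spontaneous birth before 34 weeks, and neither the sample size nor the planned validation of the preterm-birth algorithm uses pre-eclampsia.

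None of these replies answers the connectors. Two uses of and/or are not an obvious slip, and a reader cannot tell from them which combinations are required.

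**Conclusion.** The definition is wrong as written and should be corrected. The reduction to systolic ≥ 90, the omission of diastolic pressure and the sufficiency of any single component follow from the text alone. The literal case fraction of about 82% to 99.5% rests on the assumed means of 105 to 115 mmHg, SDs and correlations.

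Three stronger readings are tempting but not supported:

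- A reader might infer that the study will report pre-eclampsia in nearly every woman. The slip is too evident for that to be likely.
- A reader might infer that, with the label corrected, the connectors would multiply the case count by some stated factor. The article gives no frequencies from which to derive one.
- A reader might infer one particular replacement rule. The article does not contain it, and its cited definition is not shown.

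The consequence is confined to a secondary outcome and the ancillary work on it.

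**What to change.** 1. Correct the second systolic label so that it agrees with the diastolic measurement described for the study visits.
2. Replace both and/or connectors with an explicit statement of which combinations of pressure, proteinuria and severe complications make a case, reconciled with the definition cited as reference 32. Say whether the repeat requirement applies to pressure only or also to the dipstick.
3. Use that single rule for the secondary outcome and the ancillary studies, including any derived variable in the database.

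The cost is a text correction and, where a derivation exists, a matching change to it. Pressure and dipstick proteinuria are already listed for collection. The sponsor should confirm that the other components are available: 24-hour urinary protein appears only inside the definition, and the second and third visits are optional.

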#### Sample collection, processing and storage

Non-fasting blood samples will be collected at 20 (between 19 and 21) weeks of gestational age (Fig. 2). All research assistants will be trained according to specific and detailed Standard Operation Protocols (SOPs) developed for sample collection, processing and storage. One of the study coordinators was trained by the SCOPE team, to guarantee adequate understanding of all necessary procedures. A maximum of 20 mL of blood will be collected to provide serum and plasma specimens. The blood specimens will be stored in 250 μL 2-D barcoded cryovials after one centrifugation cycle for plasma specimens (2000×g for 10 min at 4 °C) and two centrifugation cycles for serum (2000×g for 10 min and 2400×g for 10 min at 4 °C). The blood samples will be processed and frozen at −80 °C within 2–4 h. The time interval between collection and freezing will be recorded for all specimens.

**Fig. 2 Fig2:**
[figure not shown]
Visits of Preterm-SAMBA Validation Phase

Although the Preterm SAMBA strategy and workflow is focussed around the analysis of blood samples, we recently reported a proof-of-concept study, which highlighted the potential use of the hair metabolome in the prediction of pregnancy complications [36]. Hair samples will also be collected at 20 weeks’ gestation. Samples (20–30 hair strands for each participant) will be collected from the occipital area, 0.5 cm away from the scalp, using blunt scissors. Then, hair will be packed in aluminium foil and stored at room temperature [36]. A unique linear barcode will be pasted on each hair package. All specimens and quality control information will be registered in the database.

#### Database

A specific database for the Preterm SAMBA Brazilian Cohort was developed together with MedSciNet, a Swedish based company specialized in the design and development of online database systems linked with biobanks management systems, similarly to the database previously used for the SCOPE. The preterm SAMBA database will be centralized, secure, internet-based and FDA (United States Food and Drug Administration) and HIPAA (Health Insurance and Accountability Act of 1996, United States Security and Privacy Rules) compliant, which allows continuous data entry and monitoring of study progress. Completeness of clinical data and specimen collection will be constantly monitored, with incomplete fields ‘flagged’ for attention. The database allows several monitoring procedures with hierarchical access licenses and tracking system for all specimen aliquots stored. To comply with biobank regulatory issues, patients will only be identified by a unique study number. Pseudo-anonymised metadata and interim data will be stored using our laboratory information management system. The identifying information about participants will be kept in a separate and secure local database.

#### Data and sample quality

Several procedures to enhance and assure data and sample quality will be adopted. All entered data will be prospectively and retrospectively monitored. During data entry, internal consistency of variables is performed and error messages are automatically flagged. After completing the collection of data from a participant, all information needs to be reviewed by a local monitor. Then, the final form has to be signed by the local principal investigator (PI) in order to be incorporated in the final database. The coordinating centre (Campinas, Brazil) will also perform a centralized monitoring of data and samples. An initial meeting with all researchers from Brazilian participating centres has been held to discuss the final protocol, procedures to be implemented, their particular characteristics and necessary approaches to be used to guarantee the implementation of the study. Another general meeting at the end of study is planned in order to discuss results, strategies for manuscripts’ writing and submission and other related topics.

The coordinating centre will randomly select approximately 10 % of printed completed forms to carry out a check and validation of data from the forms and database entry during the first and second half of the study. This double-check procedure enhances data quality and decreases typing errors.

The record of information regarding sample collection, processing (precentrifugation and centrifugation) and storage processes will follow the Standard Preanalytical Coding for biospecimens (SPRECs) protocol, developed and recommended by the International Society for Biological and Environmental Repositories Biospecimen (ISBER) Science Working Group [37]. This protocol enables standardization of preanalytical information, using standard codes to refer to the techniques and conditions to which the samples were submitted.

#### Metabolomics analysis

The precise methodology to be used in the validation phase will depend on the ongoing discovery studies. As detailed above we anticipate that it will be based on a targeted triple quad MS (QQQ-MS) platform, as previously described [38]. We will subsequently describe details relating to metabolomics analysis techniques and metabolomics statistical analyses. We anticipate that data analysis will be integrated into the relational database such that decision rules may combine both clinical and spectrometric data.

The performance of the final algorithm developed in the discovery phase will be evaluated by its capacity to predict spontaneous preterm birth occurrence in women from the Brazilian cohort. The validation will be performed using the average squared difference between predicted and observed outcome (R^2^), adjusted R^2^ (same as R^2^, but penalizes for the number of predictors), sensitivity, specificity, positive and negative predictive values, likelihood ratio and the area under the ROC curve.

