**Methods/design:**

Preterm SAMBA study consists of a discovery phase to identify biophysical and untargeted metabolomics from blood and hair samples associated with preterm birth, plus a validation phase to evaluate the performance of the predictive modelling. The first phase, a case–control study, will randomly select 100 women who had a spontaneous preterm birth (before 37 weeks) and 100 women who had term birth in the Cork Ireland and Auckland New Zealand cohorts within the SCOPE study, an international consortium aimed to identify potential metabolomic predictors using biophysical data and blood samples collected at 20 weeks of gestation. The validation phase will recruit 1150 Brazilian pregnant women from five participant centres and will collect blood and hair samples at 20 weeks of gestation to evaluate the performance of the algorithm model (sensitivity, specificity, predictive values and likelihood ratios) in predicting spontaneous preterm birth (before 34 weeks, with a secondary analysis of delivery before 37 weeks).

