Several Standard Operating Procedures (SOP) for sample preparation by removal of proteins via ultrafiltration were developed and validated. The analysis of deproteinized plasma samples will be performed employing gas chromatography and liquid chromatography mass spectrometry (GC-MS and LC-MS). GC-MS and LC-MS techniques will be performed as described previously [30, 31]. Quality control samples (acquired by pooling plasma from all subjects) will be interspersed in every 5th run to assess reproducibility and validity. It is envisaged that the socioeconomic/physical/biomarker discovery phase of the Preterm SAMBA study will identify several candidate markers and predictive multivariate models. Discriminatory metabolites will be translated to a targeted triple quad MS (QQQ-MS) platform, to be used in the validation phase.

The proportion of pregnancies complicated by any preterm birth is approximately 10 %. Preterm SAMBA Discovery Phase will randomly select 100 women (*n* = 100) whose pregnancies reached term as compared to fifty randomly sampled pregnancies (*n* = 50) complicated by spontaneous preterm birth prior to 37 weeks gestation, in each of the Cork Ireland and Auckland New Zealand SCOPE cohorts (Fig. 1). The 20th week samples and data will be analysed to identify sPTB potential predictors. Considering there were no previous studies on this topic for preterm birth, these numbers were empirically estimated using a similar study performed for preeclampsia [31]. Using a type I error of 0.01, type II error of 0.10, a ratio between controls and cases of 1:1, an AUC of 0.9 and an OR of 10, the estimated sample of preterm birth is 49. We then anticipated around 50 preterm birth for each of the two centers.

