### Validation phase – the Brazilian multicentre cohort study

The Preterm SAMBA validation phase consists of a Brazilian multicentre cohort study with 1150 low-risk pregnant nulliparous women. Five of the 27 members of the Brazilian Network for Studies on Reproductive and Perinatal Health (BNSRPH), were chosen to participate in the Brazilian cohort (Table 3). Previous excellence performance in epidemiological and translational studies and diversity of cultural, ethnical and sociodemographic population characteristics were criteria for centre selection. Therefore, there are participating centres in three of the five regions of Brazil, which are the three most populated regions of the country: Northeast, Southeast and South.

**Table 3 Tab3:** Participating centres in the Preterm-SAMBA study validation phase – Brazilian cohort

Maternity of CAISM, University of Campinas, in Campinas, São Paulo.	
Maternity of the School of Medicine from UNESP, in Botucatu, São Paulo.	
Maternity of the Clinic Hospital, Federal University of Rio Grande do Sul, in Porto Alegre, Rio Grande do Sul.	
Maternity of the Clinic Hospital, Federal University of Pernambuco, in Recife, Pernambuco.	
MEAC – School Maternity of the Federal University of Ceará, in Fortaleza, Ceará.	

Assuming a type I error rate, α, of 5 % and an estimated area under ROC curve of at least 0.68, then in order to test hypotheses to a suitable level of power (80 % power, β = 0.2), the sample size sufficient should approximate to 80 cases of spontaneous preterm birth (<34 weeks gestation), calculated using MEDCALC®. Based on a minimum expected preterm birth rate of 7 %, the total cohort size should therefore be of approximately 1150 subjects, around 230 women at each participating centres.

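### The planned squared-difference measure needs absolute risks, but the plan does not say how predictions from a discovery sample with 33–50% cases are put on the scale of a cohort with about 7% events

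*Protocol article*

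**What the plan says.** The algorithm comes from an outcome-enriched sample. The abstract (Methods/design) "will randomly select 100 women who had a spontaneous preterm birth (before 37 weeks) and 100 women who had term birth". The Discovery phase section instead sets 100 term pregnancies "as compared to fifty randomly sampled pregnancies" with spontaneous preterm birth in each of the two SCOPE cohorts, although its sample-size calculation uses "a ratio between controls and cases of 1:1". Cases are therefore 50% of the sample on one description and 33% on the other.

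The Validation phase section plans a cohort of about 1150 from an "estimated area under ROC curve of at least 0.68", some 80 cases of spontaneous birth before 34 weeks, and a minimum expected rate of 7%.

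The Metabolomics analysis section evaluates the final discovery-phase algorithm in that cohort: "The validation will be performed using the average squared difference between predicted and observed outcome". It labels this quantity R². It then lists adjusted R² (described as the same quantity with a penalty for the number of predictors), sensitivity, specificity, predictive values, likelihood ratio and AUC. The article mentions neither an adjustment for the sampling ratio nor a calibration measure. The same section says that the precise validation methodology depends on the discovery work and that the statistical analyses will be described later.

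**The concern.** A squared difference between prediction and outcome rewards predicted risks of the right absolute size. In a logistic-type model fitted to case–control data, the slopes carry over to the population but the intercept reflects the sampling ratio. Used unchanged in a cohort with 7% events, such a model gives risks that are several times too high, and the first measure on the list would then reflect the sampling design more than the markers. A good algorithm could be reported as worse than none.

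The label adds to the problem. A mean squared difference improves as it falls; R² improves as it rises. The text treats them as one quantity, and the two readings lead to very different results here.

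**Working it through.** **The plan's own figure.** 80 cases / 0.07 = 1143, which the plan rounds to 1150; 1150 × 0.07 = 80.5. So 7% is the event rate at which the main outcome is planned.

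**Inputs.** Event rate p = 0.07 and AUC 0.68 (Validation phase section); AUC 0.90 (the planning value in the Discovery phase section); case share q in the discovery sample = 0.50 (1:1) or 0.333 (1:2). The model form is my assumption: one normally distributed marker with equal variance in both groups, for which a logistic model is exactly right.

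**Formulas.**
- Separation of cases from non-cases: d = √2 × Φ⁻¹(AUC), which is 0.661 at AUC 0.68 and 1.812 at AUC 0.90.
- Predicted risk r at marker value x: logit r = ln[q/(1−q)] + d·x − d²/2.
- Excess on the logit scale: ln{[q/(1−q)] / [p/(1−p)]}. For 1:1 this is ln(1/0.0753) = 2.59; for 1:2 it is ln(0.5/0.0753) = 1.89.
- Mean squared difference: p × E[(1−r)² in cases] + (1−p) × E[r² in non-cases], by numerical integration.
- Reference, everyone given the average risk: p(1−p) = 0.07 × 0.93 = 0.0651.
- Scaled R² = 1 − (mean squared difference)/0.0651.

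**Worked case, AUC 0.68.**
- Unadjusted 1:1: 0.07 × 0.2252 + 0.93 × 0.2252 = 0.225. Mean predicted risk is 46%. Scaled R² = -2.46.
- Unadjusted 1:2: 0.07 × 0.3886 + 0.93 × 0.1089 = 0.128. Scaled R² = -0.97.
- Intercept matched to 7%: 0.07 × 0.8140 + 0.93 × 0.0065 = 0.063. Scaled R² = +0.03.

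In 3000 simulated cohorts of 1150, the unadjusted 1:1 score was 0.225 (95% range 0.217 to 0.233), so chance does not explain the gap.

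| AUC | Scaled R², 1:1 unadjusted | 1:2 unadjusted | Intercept matched |
|---|---|---|---|
| 0.68 | -2.46 | -0.97 | +0.03 |
| 0.80 | -1.80 | -0.72 | +0.12 |
| 0.90 | -0.96 | -0.28 | +0.30 |
| 0.95 | -0.35 | +0.09 | +0.48 |
| 0.99 | +0.43 | +0.60 | +0.76 |

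**Lower event rate (assumption).** At 3% events, 1:1 sampling and AUC 0.68, scaled R² is -6.7. The unadjusted score stays at 0.225 while the reference falls to 0.03 × 0.97 = 0.0291.

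**The other reading of R².** If R² means the squared correlation between prediction and outcome, the unadjusted 1:1 model at AUC 0.68 and 7% gives 0.028, against 0.032 with the intercept matched. No failure would be seen.

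**Which rate to correct to.** Discovery cases are births before 37 weeks; the main validation outcome is birth before 34 weeks. Suppose 2% deliver spontaneously before 34 weeks and the intercept is set to a <37-week rate of 5% to 7% (all assumed; the article gives no SCOPE rates). At AUC 0.68, scaled R² is then -0.05 to -0.16, against +0.01 with the matching rate. Correcting to the wrong outcome's rate can still leave the model scoring below no model.

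**The case against.** The strongest reply is that unadjusted scoring is inferred from silence. This is a condensed article, its Metabolomics analysis section defers the methodology and the statistical analyses, and an intercept update is the kind of step that a full analysis plan holds. The article also never names logistic regression; it speaks of multivariate models and decision rules, and the assay moves to a targeted platform between phases. This stands: a reader might infer that the plan commits to scoring raw case–control probabilities, and the article does not say so. What remains is that the section does not defer the measures. It lists them, puts a calibration-dependent one first, applies it to an algorithm from a case–control sample, and misnames it.

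A reader might also infer that predictive values are distorted by the sampling ratio. They are not: in a cohort, at a given cut-off, PPV and NPV are estimated directly, as are sensitivity, specificity and likelihood ratios. Only the meaning of a carried-over probability cut-off is affected, because it would no longer correspond to that absolute risk.

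Finally, the affected measure is not the main one. The validation sample size rests on AUC, and the abstract lists sensitivity, specificity, predictive values and likelihood ratios. That limits the consequence but does not remove it.

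**Conclusion.** The point holds in conditional form. The plan names a measure that needs absolute risks, for an algorithm built where 33–50% are cases and tested where about 7% have events, without saying how the risks are put on the cohort's scale. If probabilities are carried over unadjusted and the measure is the mean squared difference as written, a correct model scores well below no model at both AUC values in the document and under both sampling ratios: scaled R² is -2.46 or -0.97 at AUC 0.68, and -0.96 or -0.28 at AUC 0.90.

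The result rests on a logistic-type model and on an AUC below about 0.95; above that the sign turns, first for 1:2 sampling. The documents therefore do not support saying that the validation will fail. Event rates below 7% are assumptions and only widen the gap. The planned AUC analysis is untouched. This should be settled before the validation outcomes are analysed.

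**What to change.** 1. Before the algorithm is applied in Brazil, put its predicted risks on the population scale by adding ln{[π/(1−π)] × (controls/cases)} to the intercept. Take controls and cases from the actual discovery counts, and π from the source cohorts (Cork and Auckland SCOPE). At π = 0.07 the term would be -2.59 for 1:1 and -1.89 for 1:2.
2. Use a π for the outcome being validated: one intercept for birth before 34 weeks and another for birth before 37 weeks. For the <34-week version this assumes that slopes fitted to <37-week cases carry over; the calibration slope will test that.
3. Define the squared-error measure as a Brier score, or a scaled Brier score against p(1−p), and stop calling it R².
4. Report it with calibration-in-the-large and calibration slope. If the Brazilian event rate differs from that of the source cohorts, some miscalibration will remain, and these two measures will show it.
5. If a probability cut-off is used, state whether it refers to the corrected scale.

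The cost is a few sentences in the analysis plan and a few lines of code. No new data are needed, and the AUC, sensitivity, specificity, likelihood ratio and predictive value analyses do not change.
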